### Study monitoring

Proper conduct of data collection in the trial will be monitored via on-site visits of a monitoring staff member throughout the study; quality of data collected will further be monitored regularly by a statistical supervision team. After the first five participants per site are included, the quality of data (on item/trial level) per participant will be checked, aiming at detecting any error that may occur in the beginning of the project and to prevent these errors from recurring. After including participant numbers 5 to 10, the completeness and accuracy of the data on summary/scale level will be checked for all participants. Thereafter, data on a summary/scale level will be checked randomly for 1 in 5 participants. Outcomes of this data check will be written in an overview and reported to all research personnel. If adjustments to the database or procedures need to be made, these will be made as soon as possible. Moreover, the investigators will permit quality data checks, audits, and inspections by providing the sponsor direct access to source data and other documents (e.g., medical files) by request.

In each participating center, the PI will be responsible for the local ethics application, on-site training of clinicians, identification and recruitment of participants including randomization, data collection according to the study protocol, completion of the case report forms including answering queries, maintaining and updating the investigator site file, participation in monitoring, and reporting SAEs to the study PI in Barcelona. Each site will have regular meetings with their clinical team in order to ensure progress of the trial. As the leading coordinator center and with the aim of monitoring the study progress, the VHIR team will arrange telephone meetings with the local sites throughout the project on a regular basis.

Due to the need for research groups to share their data to maximize the value of each research contribution, to pool them to address research questions that require larger numbers, or to carry out meta-analyses, participants and, if applicable, their legal guardians will be asked whether they consent that their data (or portions of their data) will be shared in anonymized fashion with other research projects.

### Statistical analysis

Primary outcome measures will be analyzed by applying logistic regression analyses with type of treatment, diagnostic group (e.g., ADHD, BPD, or both), gender, and center as independent variables. A sample size of 180 participants will allow for detection of an odds ratio of 2.55 with 90% power, assuming a response rate of 20% for the CG at a significance level of 0.05. For simplification purposes, calculations will assume no effects of the covariates on the response rate. Secondary analyses will be performed on the secondary outcome measures assessed at the different time points. General linear models will be applied to examine effects of treatment group on continuous outcome variables while controlling for baseline assessment, gender, diagnostic group, and center. Categorical outcome measures will be investigated using generalized linear models. Treatment effects and their 95% confidence intervals will be reported. To investigate potential long-term effects of probiotics, data of the EG for 10 weeks will be analyzed. General linear models for repeated measurements will be applied to study changes from baseline to follow-up visit for this group, and missing data will be handled by the last observation carried forward method. Statistical significance will be defined at the 0.05 level.

Once the primary and secondary outcome measures results are obtained, all responsible investigators at all study sites will get access to the data to be able to reanalyze the data regarding specific additional research questions.

In case of an external request for replication, the respective statistical analysis will be provided by the trial statistician.

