### Study population and recruitment

Participants will be eligible for participation in this study if they meet all the inclusion criteria and none of the exclusion criteria listed in Table 1. With the aim of gender balancing the study, at least 30% female participants will be included.

**Table 1 Tab1:** Inclusion and exclusion criteria of the PROBIA trial

Inclusion criteria	Both males and females aged 18–65 years
	A high level of multidimensional impulsivity based on both a Clinical Global Impression–Severity Scale (CGI-S) score ≥ 4 and an Affective Reactivity Index (ARI) ≥ 5
	DSM-5 criteria for attention deficit/hyperactivity disorder (ADHD) and/or borderline personality disorder (BPD) confirmed by a structured diagnostic interview (ADHD: Diagnostic Interview for Adult ADHD [DIVA 2.0]; BPD: Structured Clinical Interview for DSM-IV [SCID-II])
	Deemed reliable and compliant with the protocol by the investigator
	Ability to speak and comprehend the native language of the country in which the assessments take place
	Informed consent signed
Exclusion criteria	Antibiotherapy within the last 6 weeks prior to study
	Currently taking probiotics
	Presence of a major psychiatric disorder with psychotic symptoms or other major psychiatric conditions requiring hospitalization (e.g., significant mood disorders)
	Neurological disorders involving central functions (e.g., epilepsy, multiple sclerosis, narcolepsy)
	Intelligence quotient (IQ) < 70 (measured by WAIS, if available)
	Major physical illnesses of the cardiovascular, endocrine, pulmonal, immune, or gastrointestinal system or undergoing immunosuppression
	History of/present clinically relevant somatic acute or chronic disorders that, in the opinion of the investigator, might confound the results of tolerability/safety assessments or prohibit the patient from completing the study or would not be in the best interest of the patient
	Documented allergy, hypersensitivity, or intolerance to any of the ingredients of the intervention
	Subject has taken another investigational product or taken part in a clinical study within 30 days prior to entering the study.

*Abbreviations: DSM Diagnostic and Statistical Manual of Mental Disorders*, *PROBIA* Treatment of impulsivity in adults with probiotics, *WAIS* Wechsler Adult Intelligence Scale

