### Outcome measures

#### Primary outcomes

The primary outcome measure will be response to treatment, defined by a reduction in the Affective Reactivity Index–Self-Report (ARI-S) scale total score of at least 30% compared with baseline plus a Clinical Global Impression–Improvement Scale total score of 1 or 2 (very much improved or much improved) at the end of the placebo-controlled phase.

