*Abbreviations: ADHD* attention-deficit/hyperactivity disorder, *ADHD-RS* Attention-Deficit/Hyperactivity Disorder Rating Scale, *ARI-S* Affective Reactivity Index–Self-Report, *BPD* borderline personality disorder, *CGI-I* Clinical Global Impression–Improvement Scale, *CGI-S* Clinical Global Impression–Severity Scale, *CPT-II* Continuous Performance Test, *DERS-16* Difficulties in Emotion Regulation Scale, *DIVA 2.0* Diagnostic Interview for Adult ADHD, Second Edition, *FAST* Functioning Assessment Short Test, *IQ* intelligence quotient, *M.I.N.I.-Plus* Mini-International Neuropsychiatric Interview, *PROBIA* Treatment of impulsivity in adults with probiotics, *ProMAS* Probabilistic Medication Adherence Scale, *PSS* Perceived Stress Scale, *SCID-II* Structured Clinical Interview for DSM-IV Axis II Disorders, *SDQ* Strengths and Difficulties Questionnaire, *SES* socioeconomic status, *UPPS-P* Urgency, Premeditation (lack of), Perseverance (lack of), Sensation Seeking, Positive Urgency, Impulsive Behavior Scale, *WAIS* Wechsler Adult Intelligence Scale, *Y-BOCS* Yale-Brown Obsessive Compulsive Scale

At the screening visit (TS), the rate of impulsivity will be established by performing structured interviews, the ARI-S, and the Clinical Global Impression–Severity Scale. After having established the presence of high impulsivity, the diagnosis of ADHD and/or BPD will be assessed via the Diagnostic Interview for Adult ADHD, Second Edition, and the Structured Clinical Interview for DSM-IV Axis II Disorders section for BPD, respectively. Thereafter, screening for eligibility based on clinical history, demographics (including SES), tests, and questionnaires (e.g., Mini-International Neuropsychiatric Interview [M.I.N.I.-Plus], IQ tests [Wechsler Adult Intelligence Scale, Fourth Edition]) will be performed, and informed consent will be obtained. Once this process is finished, a mobile health system as well as a food record will be introduced to participants (duration, approximately 1 h). The mobile health system will enable patients to share (via a mobile application) data of interest regarding their physical activity (acceleration, number of steps).

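### The primary logistic model omits baseline ARI-S and CGI-S: a modest, cheaply avoided loss of efficiency if baseline is prognostic, not a bias

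*Protocol article*

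**What the plan says.** - **Primary model** (Protocol article, Statistical analysis): "logistic regression analyses with type of treatment, diagnostic group (e.g., ADHD, BPD, or both), gender, and center as independent variables". This is a stated list of four terms, with no baseline score among them.
- **Between-group models for continuous secondary outcomes** (same section): fitted "while controlling for baseline assessment, gender, diagnostic group, and center", that is, the same three covariates plus baseline.
- **Within-group model for the synbiotic arm** (same section): "General linear models for repeated measurements will be applied to study changes from baseline to follow-up visit for this group". No baseline covariate is stated here.
- **Primary endpoint** (Primary outcomes): a fall in ARI-S "total score of at least 30% compared with baseline plus a Clinical Global Impression–Improvement Scale total score of 1 or 2".
- **Baseline data**: at screening, impulsivity "will be established by performing structured interviews, the ARI-S, and the Clinical Global Impression–Severity Scale". Table 3 marks ARI-S and CGI-S again at T0, which the Participant timeline section calls the baseline visit.
- **Entry thresholds** (Table 1): CGI-S "score ≥ 4 and an Affective Reactivity Index (ARI) ≥ 5".
- **Allocation** (Randomization and study intervention): 1:1, stratified by center only. Balance on other characteristics is expected from the sample size.
- **Sample size** (Statistical analysis): "A sample size of 180 participants will allow for detection of an odds ratio of 2.55 with 90% power", with 20% response on placebo, significance level 0.05, and covariates assumed to have no effect.

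**The concern.** The primary comparison lacks the baseline adjustment that its continuous between-group counterparts receive, and the article gives no reason. Defining response as a percentage fall does not make response independent of the starting score. Selection on an entry threshold produces regression to the mean, whose size varies with the starting value. A 30% rule on a score with steps also sets a hurdle that depends on where the participant starts. The CGI-I half of the endpoint carries no explicit baseline term.

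If baseline severity does predict response, leaving it out gives up some power. It also leaves a chance difference in severity between the arms in the estimate. If such a difference appeared and adjustment were added only then, the adjustment would look data-driven.

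**Working it through.** **1. Setting, and the plan's own power figure.** Placebo odds are 0.20/0.80 = 0.25. Multiplied by 2.55 they give 0.6375, so response on the synbiotic is 0.6375/1.6375 = 0.389. Allocation of 180 at 1:1 gives 90 per arm. The two-sided test at 0.05 uses a pooled rate of (0.200 + 0.389)/2 = 0.295:

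- SE under the null = √(2 × 0.295 × 0.705/90) = 0.068
- SE under the alternative = √((0.20 × 0.80 + 0.389 × 0.611)/90) = 0.0665
- z = (0.1893 − 1.96 × 0.068)/0.0665 ≈ 0.84, so power is about 80.1%

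The stated 90% does not reproduce. The article does not state sidedness; a one-sided test gives 87.8%. This is a separate problem, and it matters here only because it fixes the starting point at about 80%. Expected responders: 90 × 0.20 + 90 × 0.389 = 18 + 35 = 53.

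**2. Does the 30% rule remove dependence on baseline?** Assume integer ARI-S scoring, which the article does not state.

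| Baseline ARI-S | 30% of baseline | Points needed | Actual fall required |
|---|---|---|---|
| 5 | 1.5 | 2 | 40% |
| 6 | 1.8 | 2 | 33% |
| 7 | 2.1 | 3 | 43% |
| 10 | 3.0 | 3 | 30% |

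The hurdle varies with the starting score, so some dependence is plausible. This does not give its strength or direction.

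**3. Chance imbalance.** The standardized baseline difference between arms has SD √(2/90) = 0.149. For 0.2 SD, 0.2/0.149 = 1.34, a two-sided probability of about 18%. For 0.3 SD, 0.3/0.149 = 2.01, about 4%. If the odds ratio per SD is 1.5, a 0.2 SD difference multiplies the treatment odds ratio by about 1.5^0.2 = 1.08. At 2.5 the factor is 2.5^0.2 = 1.20. Either can go in either direction.

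**4. Power gained by adjusting.** The article gives no prognostic strength, so it is varied. The first simulation had 4,000 trials per row, 90 per arm, marginal rates held at 20% and 38.9%, and one standardized baseline covariate. Diagnosis, gender and center were left out.

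| Odds ratio per SD (assumed) | Power without | Power with | Gain (points) | Conditional treatment OR |
|---|---|---|---|---|
| 1.00 | 79.4% | 79.8% | 0.4 | 2.55 |
| 1.28 | 79.6% | 79.9% | 0.3 | 2.58 |
| 1.65 | 80.1% | 81.8% | 1.7 | 2.67 |
| 2.12 | 79.7% | 84.0% | 4.3 | 2.82 |
| 2.72 | 80.2% | 86.6% | 6.4 | 3.02 |

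Type I error was 4.7–5.2% without the covariate and 4.4–5.1% with it. The Monte Carlo standard error of one power figure is √(0.8 × 0.2/4000) = 0.6 points. The two analyses share the same simulated data.

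A second one-covariate simulation (3,000 trials per scenario) gave 78.9 → 80.5% at 1.5, 80.8 → 84.5% at 2.0 and 79.7 → 84.9% at 2.5.

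The full model, with diagnosis, gender, center and two baseline terms, is closer to the proposed change. With 4,000 trials, a correlation of 0.5 between the two baselines and only one of them prognostic (both assumed), power went from 79.8 to 79.9% at 1.2, from 79.7 to 80.6% at 1.5 and from 80.1 to 83.8% at 2.0. A further full-model run with no prognostic effect gave 81.4% against 81.2%, no material loss. It gave gains of about 1 point at 1.3–1.5 and 3–4 points at 2.0–2.5.

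Taken together, the gain is about 0 to 1 points up to an odds ratio per SD of about 1.5, and about 3 to 5 points at 2.0–2.5.

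**The case against.** The case for leaving the model alone is substantial. It is prespecified, includes the stratification factor, and keeps its type I error. The endpoint is binary and already relative to baseline. Its nearest counterpart among the secondary outcomes is the categorical ones, for which the article states only generalized linear models and no baseline covariate. Nothing in the article shows that baseline ARI-S or CGI-S predicts response. The entry thresholds truncate both scales, and two mechanisms may partly cancel: regression to the mean favors high starters, but they need a larger absolute fall. Chance imbalance is ordinary randomization variation that the test already allows for. The adjusted odds ratio also differs from the one used for the sample size.

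All of this stands as a limit on the size of the point. It does not remove the point, because the change uses data already scheduled, costs no material power in the null case, and brings the primary model into line with the between-group continuous models.

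Three stronger readings are tempting, and the documents support none of them:

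- **That the primary analysis is biased or invalid.** It is not. The issue is efficiency and precision given the imbalance that occurs.
- **That every continuous secondary model adjusts for baseline.** The repeated-measures model within the synbiotic arm states no baseline covariate, so the contrast holds only for the between-group models.
- **That adjustment would rescue the stated power.** The highest simulated figure is 86.6%, at a very strong assumed effect.

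**Conclusion.** The point holds as a minor, worthwhile improvement. The primary logistic model omits two baseline measures that the trial collects, and neither the stratification nor the other covariates account directly for baseline severity. The expected benefit is about 0 to 1 points of power if baseline is weakly prognostic and about 3 to 5 points if the odds ratio per SD is 2.0 to 2.5. Adjustment also gives some protection against a chance severity difference, which has about an 18% probability of exceeding 0.2 SD.

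These figures rest on 90 per arm with no dropout, response rates of 20% and 38.9%, two-sided testing at 0.05, and an assumed prognostic strength. The omission and the availability of the data are certain from the text; the size of the gain is not. The difference between the stated 90% power and the roughly 80% recomputed needs its own correction and should not add weight to this point.

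**What to change.** Before unblinding, add T0 ARI-S total and T0 CGI-S as continuous covariates to the primary logistic regression, beside diagnostic group, gender and center. Because the treatment odds ratio then becomes conditional on baseline and is no longer the quantity in the sample-size sentence, report a covariate-standardized risk difference with its 95% CI next to it.

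The cost is one line in the analysis section and no new data. With three diagnostic groups and three centers, the slopes go from 1 + 2 + 1 + 2 = 6 to 8. Expected responders per slope therefore fall from 53/6 = 8.8 to 53/8 = 6.6. The full-model simulations with both terms included showed no material loss of power from this.

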**Methods/design:**

This is a prospective, multicenter, double-blind, randomized controlled trial with two arms: treatment with a synbiotic formula versus placebo treatment. The primary outcome is the response rate at the end of the placebo-controlled phase (response defined as a Clinical Global Impression–Improvement Scale score of 1 or 2 = very much improved or much improved, plus a reduction in the Affective Reactivity Index total score of at least 30% compared with baseline). A total of 180 participants with highly impulsive behavior and a diagnosis of attention deficit/hyperactivity disorder (ADHD) and/or borderline personality disorder, aged 18–65 years old, will be screened at three study centers. Secondary outcome measures, including changes in general psychopathology, ADHD symptoms, neurocognitive function, somatic parameters, physical activity, nutritional intake, and health-related quality of life, will be explored at assessments before, during, and at the end of the intervention. The effect of the intervention on genetics, microbiota, and several blood biomarkers will also be assessed. Gastrointestinal symptoms and somatic complaints will additionally be explored at 1-week follow-up.

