Recruitment began on 22 February 2019 and will have a duration of 2 years. A total of 180 participants (60 subjects per site) will be recruited by trained psychiatrists and/or psychologists at the different sites (see Fig. 1). Strategies aimed at optimizing the recruitment process will include the distribution of handouts or flyers to colleagues, physicians, and families, as well as an offer of reimbursement of study-related travel costs to participants. Furthermore, and depending on local regulations, information via presentations, websites, and social media campaigns will be provided. Regular calls will be made to patients to avoid participant withdrawal from the study.

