### Randomization and study intervention

After eligibility checks have been conducted and written consent has been obtained by the different psychiatrists and/or psychologists of the trial team, eligible participants will be randomized to the experimental (EG) or the control (CG) group in a 1:1 allocation ratio using an independent web-based computerized service (www.randomization.com). Randomization will be center-stratified and have a fixed length per center, being independent of participant characteristics. However, due to the large sample size, a balanced ratio of baseline characteristics between the EG and CG is expected.

Individual participant treatment kits will contain all required daily synbiotic or placebo envelopes for the 10-week RCT and will be prepared in advance by sequentially numbering and labeling them as “A” or “B.” Because this is a double-blind study, neither the participants nor the clinicians involved in the trial will have access to the randomization list.

Synbiotic 2000 Forte 400 (SF) is a synbiotic formula currently produced by Synbiotic AB in Höganäs, Sweden. Each dose (powder-containing sachet) of SF contains 100 billion of each of *Pediococcus pentosaceus* 5-33:3, *Lactobacillus paracasei subsp. paracasei* 19, *Lactobacillus plantarum* 2362, and *Leuconostoc mesenteroides* 77:1, in combination with four bioactive fermentable fibers (2.5 g each of β-glucan, inulin, pectin, and resistant starch). SF is categorized as a generally regarded as safe agent, being tested on several hundreds of critically ill patients (e.g., pancreatitis, liver transplant) with no side effects or specific and/or relevant risks conferred to the trial participants [83]. The placebo (also provided by Synbiotic AB) is composed of the polysaccharide maltodextrin and has a texture and flavor similar to SF. Participants will be asked to continue with their previous medications and/or usual treatments and add the synbiotic or placebo once daily on top of cold foods such as yogurt, muesli, or salad. To secure bacterial viability, participants will be asked to store both SF and placebo at + 4–6 °C.

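### The stated 90% power is wrong: on the protocol's own inputs, 180 participants give about 80% power for an odds ratio of 2.55

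*Protocol article*

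**What the plan says.** The sample size justification is in the Statistical analysis section of the protocol article: "A sample size of 180 participants will allow for detection of an odds ratio of 2.55 with 90% power". The control rate and alpha behind this claim are a 20% response in the control group and 0.05. The same section says that covariate effects on response are ignored in the calculation. It also gives the general significance rule, "Statistical significance will be defined at the 0.05 level", and the reporting rule, "Treatment effects and their 95% confidence intervals will be reported". It does not say whether the test is one-sided or two-sided.

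Under Randomization and study intervention, participants are "randomized to the experimental (EG) or the control (CG) group in a 1:1 allocation ratio", so 180 means 90 per arm. Under Study population and recruitment, 180 is the intake: "A total of 180 participants (60 subjects per site) will be recruited". The Abstract (Methods/design) instead says that the 180 participants "will be screened at three study centers".

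**The concern.** Every input to the power calculation is printed, so the 90% can be checked directly, and it does not follow from those inputs. This is a stated figure that is wrong. It is not a detail left to a fuller document.

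The figure is the design justification for the primary outcome. If the true power is about 80%, the chance of missing the odds ratio the trial was sized for is about one in five, where the article implies one in ten. Readers of a null result would credit the trial with more sensitivity than it has, and the wrong figure is likely to be repeated in the results paper.

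**Working it through.** **Inputs, all from the protocol article**

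- Total of 180, odds ratio 2.55, control response 20%, significance level 0.05, no covariate effects (Statistical analysis).
- 1:1 allocation, hence n = 90 per arm (Randomization and study intervention).
- Two-sided test: an assumption, because sidedness is not stated. It is supported by the planned 95% confidence intervals. One-sided results are given below.

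With no covariate effects, the logistic regression reduces to a comparison of two proportions.

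**Step 1. Response rate in the synbiotic group**

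p2 = (0.2 × 2.55) / (0.8 + 0.2 × 2.55) = 0.51 / 1.31 = 0.3893. The difference is 0.1893 and the mean rate is 0.2947.

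**Step 2. Attempt to reproduce 90%, two-sided 0.05**

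- Standard error under the null (pooled): √(2 × 0.2947 × 0.7053 / 90) = 0.0680.
- Standard error under the alternative: √((0.2 × 0.8 + 0.3893 × 0.6107) / 90) = 0.0665.
- Power = Φ[(0.1893 − 1.96 × 0.0680) / 0.0665] = Φ(0.844) = **80.1%**.

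Other two-sided methods on the same inputs:

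| Method | Power |
|---|---|
| Unpooled variance | 81.3% |
| Wald test on log odds ratio: ln 2.55 = 0.936, SE 0.341, Φ(0.786) | 78.4% |
| Arcsine | 80.5% |
| Chi-square, exact enumeration | 80.4% |
| Likelihood ratio, exact enumeration | 80.5% |
| Fisher or continuity-corrected | 75.8% |

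None gives 90%.

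**Step 3. Other readings of the statement**

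| Reading | Power |
|---|---|
| One-sided 0.05, pooled | 87.8% |
| One-sided 0.05, unpooled | 88.5% |
| One-sided 0.05, Wald | 86.5% |
| 180 per arm, two-sided | 97.8% |
| 2.55 as a risk ratio (20% v 51%) | 99.4% |
| 20% as the higher of the two rates | 56.1% |

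None gives 90%.

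**Step 4. What the inputs do fit**

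Required size per arm = [(z_α √(2 × 0.2947 × 0.7053) + z_β √(0.2 × 0.8 + 0.3893 × 0.6107)) / 0.1893]².

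- 80% power, two-sided: 89.8, rounded up to 90 per arm, **180 in total**.
- 90% power, two-sided: 119.8, rounded up to 120 per arm, **240 in total**.
- 90% power, one-sided: 97.4, rounded up to 98 per arm, 196 in total.

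The two-sided odds ratio detectable with 90 per arm is 2.548 at 80% power and 2.91 at 90% power (20% v 42.1%). The first rounds to the article's 2.55.

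**Step 5. Missing outcomes (illustration only)**

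The article gives no attrition rate. If 180 are randomized and a fraction, assumed here, have no response status at T2, pooled complete-case power is 75.7% at 10% loss (81 per arm), 73.3% at 15% (76.5 per arm) and 70.7% at 20% (72 per arm).

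**The case against.** The best defence is that the article never says the test is two-sided. A one-sided 0.05 calculation with unpooled variance gives 88.5%, which someone might round to 90%. This does not rescue the figure. No one-sided method reaches 90%, one-sided 90% power would need 196 participants, and the planned 95% intervals correspond to a two-sided 0.05 test.

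Three other objections have some force.

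- The attrition figures rest on assumed rates, and a journal article may leave a dropout allowance to the full protocol. They show how sensitive the power is and are not part of the error.
- Whether 180 counts people screened, recruited or randomized is a separate wording question that only the sponsor can settle.
- What a null result rules out is read from the confidence interval, which the article commits to reporting. The harm is therefore a misstated type II error. The endpoint, the analysis model and the type I error are unaffected.

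It is also fair to say that the sponsor's own calculation is not shown. The close match at 80% suggests that 90% was written where 80% had been calculated, but does not prove it.

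**Conclusion.** The power statement is wrong as written. With 90 per arm, 20% versus 38.9% and two-sided 0.05, power is about 80% (78.4% to 81.3% across the pooled, unpooled and Wald formulas), roughly 10 percentage points below the stated figure. The type II error at the design effect is about 20%, not 10%. The only assumption beyond the printed inputs is two-sidedness, and dropping it still leaves power short of 90%. The result also supposes that all 180 contribute a primary outcome. Any loss, or a reading of 180 as the number screened, lowers power further.

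**What to change.** Correct the sentence in the Statistical analysis section so that its figures agree, and state that the test is two-sided. The options are:

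1. Keep 180 and the odds ratio of 2.55, and state 80% power (90 per arm, 20% versus 38.9%, two-sided 0.05). This fits the printed inputs best.
2. Keep 180 and 90% power, and state a detectable odds ratio of about 2.9 (20% versus 42%).
3. If 90% power for 2.55 was the real design target, the total would have to be 240, which is 60 more than planned.

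Options 1 and 2 cost wording only. They make the stated sensitivity less favourable and add no participants. Option 3 is a real design change, in a trial that had already begun recruiting.

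In the same edit, the sponsor should say whether 180 is the number screened, recruited or randomized, align the Abstract with Study population and recruitment, and give the power at the number expected to have T2 data.
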